### Randomisation and blinding

Participants will be block-randomised, with block sizes generated using a randomisation programme. The programme will randomly assign patients into either a control group or intervention group through a random block size (the block size is 4, 6, 8 or 10 patients). Eligible and consented patients will be block-randomised in a ratio of 1:1. No effort will be made to stratify the subgroups considered in the secondary analyses. By the nature of the intervention, CURE cannot be double-blinded. Un-blinding is not applicable due to the nature and setting of the intervention.

All patient data collected are de-identified using a single patient numbering system. Patients are assigned to a study number to ensure no bias in the results. This system will be a simple incrementing scheme, such that patients randomised into the CURE trial are identified as study-001, study-002, etc.

### Ventilation settings, oxygenation, and patient positioning

#### Tidal volumes (V_T_) and driving pressures (DP) during MV

The V_T_ is adjusted to 6–8 ml/kg per ideal body weight (IBW), and the maximum minute ventilation (V_Emax_) to ≤ 0.2 L/kg/min. The IBW is measured using the patient’s height and look-up table at the bedside or is calculated using the formulae:

1$$ \mathrm{Men}:50+0.91\times \left(\mathrm{height}\ \left[\mathrm{cm}\right]-152.4\right)\ \mathrm{kg} $$
2$$ \mathrm{Women}:45.5+0.91\times \left(\mathrm{height}\ \left[\mathrm{cm}\right]-152.4\right)\ \mathrm{kg} $$

The DP is the plateau pressure (P_Plat_) minus the PEEP. In patients with very severe ARDS the adjustment of V_T_ to 6–8 ml/kg IBW may be injurious if the DP is higher than 15 cmH_2_O. A DP ≤ 15 cmH_2_O was associated with better patient survival when assessed using a multilevel mediation analysis of 3562 patients in nine RCTs of ARDS [28]. Therefore, the DP will be limited to ≤ 15 cmH_2_O at all times. In addition, during spontaneous ventilation, pressure support will be limited to ≤ 15 cmH_2_O.

The ventilation rate is set between 12 and 20 breaths per minute. The aim is to keep the plateau pressure P_plat_ ≤ 30 cmH_2_O. If necessary, V_T_ may be reduced to as low as 4 ml/kg and the respiratory rate (RR) kept at ≤ 30 breaths per minute. CO_2_ will frequently rise in severe lung injury (permissive hypercapnia) when patients are mechanically ventilated within these guidelines. However, if CO_2_ is ≥ 80 mmHg or increased by ≥ 50% in the previous 4 h, the intensive care specialist on duty will be notified, and they may choose to deviate from these guidelines.

#### Ventilation mode

All patients enrolled are to be ventilated using a pressure-controlled mode, for example, the Bi-Level ventilation mode on the Puritan Bennett PB840 ventilator (Covidien, Boulder, CO, USA) or PC-SIMV+ on the Dräger Evita® Infinity® V500. Patients will be ventilated using Bi-Level/PC-SIMV+ mode, which allows unrestricted spontaneous breathing efforts to lessen ventilator dyssynchrony. However, during any recruitment manoeuvre procedures, synchronized intermittent mandatory ventilation (SIMV) with pressure-controlled (PC) ventilation is used and returned to original mode afterwards. Should patients already be ventilated using a ventilator incompatible with the CURE computer system, they will have their ventilator changed to a compatible ventilator for the trial. Patients will be transitioned to assisted spontaneous breathing (ASB) if they meet the weaning criteria (see “Weaning”).

In severe ventilator dyssynchrony, a very high respiratory drive may result in sub-atmospheric circuit pressures and risk of aspiration of gastric contents around the endotracheal cuff. If a participant has a high respiratory drive on Bi-Level/PC-SIMV+ ventilation, producing a fall in airway pressure during inspiration, muscle relaxants will be considered to facilitate controlled breathing. However, if the clinician feels the participant may benefit from breathing spontaneously, transition to ASB may be made if they substantially meet the weaning criteria (see “Weaning”).

However, spontaneous breathing efforts may mask high trans-pleural pressures and produce high levels of regional lung strain. Oesophageal pressure will not be measured during this trial. If the treating clinician is concerned about patient self-inflicted lung injury (P-SILI) [29, 30], they will consider using muscle relaxants to control ventilation.

Patients will not undergo any procedures using a cough-assist machine prior to weaning and transitioning to spontaneous breathing. However, the treating clinician may use a cough-assist machine to aid secretion removal (during spontaneous breathing) if they believe it is in the patient’s best interests. Finally, in any circumstances where the patient is planned to be temporarily disconnected from the ventilator, their endotracheal tube will be clamped to prevent de-recruitment.

#### SpO_2_ targets

To ensure a fair comparison, all CURE study participants will have inspired oxygen levels titrated to achieve the following pulse oximetry saturations:
i.SpO_2_ = 93–95% if FiO_2_ is less than 60%ii.SpO_2_ = 90–92% if FiO_2_ is greater than or equal to 60%

The aim is to spend greater than or equal to 90% of time in the target range. The FiO_2_ should only be increased above 21% if these targets are not met, using 5% increments starting with a FiO_2_ = 25%. There is natural variability in SpO_2_. To avoid toggling between two FiO_2_ levels, 10 min of settling time will be allowed before changing the FiO_2_. The best FiO_2_ is chosen to keep the saturation within the specified targets ranges over 90% of the time.

#### Patient position, turning and prone positioning

Patients are kept at 30° head up whenever possible. This position maximises recruitment of the lung and may reduce the risk of aspiration. Wherever possible, patients should be rolled from supine to right-side down, back to supine, then to left-side down. This turning of patients is ideally performed every 3 h.

Transient hypoxaemia frequently occurs after a patient has been turned and may be worse if there is inadequate PEEP. Hypoxaemia may also become more severe if participants are rolled from left-side down to right-side down due to cyclical de-recruitment of the non-dependent lung and re-recruitment of the dependent lung. This cyclical de-recruitment of the lung has the potential to contribute to VILI. Thus, patients with severe lung injury may be very intolerant of being turned. In some instances, the lungs may need to be re-recruited. If desaturation does occur, this will be recorded as a serious adverse event (SAE).

Prone positioning of patients may be considered if the P/F ratio is ≤ 100 and FiO_2_ ≥ 60%. Patients randomised to the intervention arm (MBV) may still undergo a protocolised recruitment manoeuvre. For patients in the standard practice ventilation arm (SPV) a staircase recruitment manoeuvre is left to clinical judgement.

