### Adverse event (AE) and SAE reporting

(AEs are defined as any unexpected change in physiology in a study participant associated with either the RM_max_ or PUMP. This does not necessarily have to have a causal relationship with the aforementioned procedures. Typically, this would be an unexpected, non-life-threatening event, which rapidly resolves following simple corrective measures. For example, hypotension will occur in most participants undergoing an RMmax or PUMP. However, if the procedure had to be shortened or abandoned, but the participant recovered with simple corrective measures (e.g. temporarily increasing noradrenaline by ≥ 5 mcg/min) or giving > 500 ml fluid bolus) this would be recorded as an AE. It is very important these events are accurately recorded as risk factors for AEs that need to be defined when carrying out RMs (as seen in Additional file 3).

SAEs are defined as any untoward medical occurrence that (1) results in death; (2) is life-threatening; (3) prolongs hospitalisation or (4) results in disability or incapability. However, baseline mortality in the patients in intensive care who are enrolled in the trial will likely be high due to the critical illness necessitating admission to the ICU. Despite attempts at prevention, trial participants will frequently develop life-threatening organ failure(s) unrelated to study interventions. Events that are a part of the natural history of the primary disease process or expected complications of critical illness will not be reported as SAEs in this trial. Additionally, events already defined and reported as study outcomes, such as mortality or re-admission to the ICU, will not be labelled and reported separately as SAEs unless they are considered to be causally related to the study intervention or are otherwise of concern in the investigator’s judgement.

SAEs will be reported to the principal investigator within 24 h of any investigator becoming aware of the event. The minimum information to report includes:
Patient trial identifierThe nature of the eventThe time the event commenced and ceasedAn investigator’s opinion of the relationship between study involvement and the event (not related, unlikely, possibly, probably or definitely related)Whether treatment was required for the event and what treatment was administered

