SAEs could include pneumothorax, hypotension leading to cardiac arrest, transient desaturation leading to severe or prolonged desaturation, tachycardia, bradycardia, arrhythmia, anaphylaxis and unintended protocol deviations.

In the unlikely event of a physical injury to the participant as a result of their participation in this study, they will be eligible to apply for compensation from the Accident Compensation Corporation (ACC) NZ within its limitations. If the participant’s family/friend have any questions about the ACC, they will be able to ask the researchers for more information before they agree to take part in this trial.

ACC cover is not automatic and their case will need to be assessed by the ACC according to the provisions of the 2001 Injury Prevention Rehabilitation and Compensation Act. If the claim is accepted by the ACC, the patient still might not receive compensation. This depends on a number of factors such as whether they are earners or non-earners. The ACC usually provides only partial reimbursement of costs and expenses and there may be no lump sum compensation payable. There is no cover for mental injury unless it is a result of physical injury. If your relative or friend has ACC cover, generally this will affect their right to sue the investigators.

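### The protocol gives conflicting SAE rules for desaturation after turning, and lists protocol deviations among its SAE examples

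*Protocol article*

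**What the plan says.** Three places in the protocol article bear on whether a desaturation is an SAE.

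- **Patient position, turning and prone positioning.** On frequency of turning: "This turning of patients is ideally performed every 3 h". On what follows: "Transient hypoxaemia frequently occurs after a patient has been turned and may be worse if there is inadequate PEEP". On reporting: "If desaturation does occur, this will be recorded as a serious adverse event (SAE"). This last sentence is mandatory and carries no threshold, duration, severity or causality condition.
- **Adverse event (AE) and SAE reporting, definition.** "SAEs are defined as any untoward medical occurrence that (1) results in death; (2) is life-threatening; (3) prolongs hospitalisation", with disability or incapability as the fourth criterion. Two exclusions follow. Under the first, events in the natural history of the disease and "expected complications of critical illness will not be reported as SAEs in this trial". Under the second, "events already defined and reported as study outcomes, such as mortality or re-admission to the ICU" are not reported separately as SAEs, unless they are judged causally related to the intervention or are otherwise of concern to the investigator.
- **Same section, examples.** The list of what SAEs could include mentions transient desaturation only where it leads to severe or prolonged desaturation. It ends with "anaphylaxis and unintended protocol deviations".

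Desaturation is a secondary outcome, with a threshold of SpO2 < 88% in the Abstract and in Study design and setting, and < 90% in Study outcome. The Data Monitoring Committee section says that the DMC is sent, and reviews, every SAE report.

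**The concern.** Staff who follow the turning section will file an SAE for each desaturation after a turn. Staff who follow the reporting section will file very few. Both rules are in force, so the classification depends on who is reporting and which section they have in mind.

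Two features make this more than untidy wording. The trial is unblinded (Randomisation and blinding), so discretion over what counts is exercised with the arm known. The turning section itself says that hypoxaemia after turning may be worse when PEEP is inadequate, and PEEP is what is randomised. The choice of rule could therefore change any comparison of SAEs between arms, as well as the total.

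Protocol deviations are a separate defect in the same list. A deviation is not an untoward medical occurrence, which is what the definition requires. The protocol already has another route for variations: they are reported to the primary investigator and followed up (Adherence to the intervention), and followed up and noted (Data management).

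**Working it through.** The check is mainly a comparison of texts. The plan gives no figure on this point to reproduce.

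**Step 1. Classify one event under each rule.** Take a brief fall in SpO2 after a scheduled turn that resolves without lasting harm.

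| Rule | Is it an SAE? |
|---|---|
| Turning section | Yes, with no condition attached |
| SAE definition | No: no death, threat to life, prolonged stay or disability |
| Exclusion of expected complications | Excluded if it counts as a complication of critical illness; no exception is attached |
| Exclusion of study outcomes | Excluded as a secondary outcome, unless causally related or of concern to the investigator |
| SAE examples | Not among those named, because it is neither severe nor prolonged |

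The first row cannot be reconciled with the second, whatever one decides about the others.

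**Step 2. Is there a middle category?** The AE definition covers unexpected changes associated with RM_Max or PUMP. Recruitment manoeuvres (RM) reserves both procedures for the MBV arm. A turning desaturation in a control patient is therefore an SAE or is not reported as an adverse event at all.

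**Step 3. Is desaturation defined?** The turning section gives no threshold. The outcome sections give two, < 88% and < 90%. The SpO2 target is 90–92% when FiO2 is 60% or more, so under the < 90% threshold any fall below the target range in those patients counts as desaturation.

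**Step 4. Scale, as an illustration only.**

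- From the protocol: turning ideally every 3 h, so 24 / 3 = 8 turns per day; 320 patients.
- Assumed, not in the protocol: 8 ventilated days per patient; 1%, 5% or 20% of turns followed by desaturation.
- Turns: 8 × 8 × 320 = 20,480.
- Reports = 20,480 × rate per turn.

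| Assumed rate per turn | Per patient-day (8 × rate) | Total reports |
|---|---|---|
| 1% | 0.08 | 205 |
| 5% | 0.4 | 1,024 |
| 20% | 1.6 | 4,096 |

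Under the reporting section, almost none of these would count unless they met a seriousness criterion or became severe or prolonged. The totals assume full adherence to a turning schedule that the protocol describes only as ideal and where possible, so they lean high for any given rate.

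**The case against.** The strongest reply has four parts.

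- **The turning sentence may be meant narrowly.** It follows remarks on patients with severe injury who tolerate turning poorly and may need re-recruitment. It says desaturation, whereas the event called frequent is transient hypoxaemia. That may be the intent, but nothing in the wording limits it, and the sentence still lacks a seriousness criterion.
- **The exclusions are not absolute.** The study-outcome exclusion has an exception for causal relation or investigator concern. Because the protocol links this hypoxaemia to PEEP, some events could qualify. Whether a desaturation provoked by turning is a complication of critical illness is also a matter of reading. Both points stand. They make the classification less certain and do not settle it.
- **The examples are illustrative.** The list says what SAEs could include. It does not make every deviation an SAE. A reader might infer that the MBV arm, with its RM_Max and regular PUMPs, will accumulate SAEs from deviations alone. The documents do not support that: they give no deviation rate and no rule requiring each deviation to be reported as an SAE.
- **The DMC can look behind a count.** It receives individual reports, each stating the nature of the event, its timing, relatedness and treatment, so it can tell a turning desaturation from a pneumothorax. A reader might infer that SAE data from this trial would be meaningless. That goes too far. No section specifies a formal comparison of SAE rates by arm, and the stopping boundary rests on mortality.

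**Conclusion.** The contradiction is real and lies in the current text; it does not arise from detail left to a fuller document. The turning section and the reporting section cannot both be followed for a brief desaturation. The SAE examples add a narrower description of desaturation and an item that the definition does not admit.

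The supported consequence is inconsistent SAE classification in an unblinded trial, for an event linked to the randomised factor, with a possibly large reporting load on the principal investigator and the DMC. The range of about 200 to 4,100 reports rests on assumed rates per turn and assumed ventilated days. It shows that the load is sensitive to the rule and is not a forecast. The contradiction itself does not depend on any rate.

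No efficacy analysis, alpha or power is touched, and the mortality boundaries in Stopping rule stand as they are. The point should be corrected, but it does not threaten the trial's main conclusions.

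**What to change.** Reconcile the turning section, the SAE definition with its exclusions, and the SAE examples into one rule that applies identically in both arms. The rule should:

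- state when a desaturation is an SAE, and have the turning section refer to that rule instead of setting its own;
- say how the two exclusions, and the exception to the second, apply to desaturation, so that an event is not admitted by one sentence and removed by another;
- use one SpO2 threshold for desaturation, resolving < 88% against < 90%.

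Desaturations that are not SAEs remain captured in the secondary outcome, because the monitor SpO2 waveform is already collected to detect them (Other patient information).

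Remove protocol deviations from the SAE examples and report them by the route already given in Adherence to the intervention and Data management. A medical event that results from a deviation would still be judged against the SAE definition in its own right.

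The cost is protocol wording and a line in staff training. Trial status says that recruitment had not begun, so no reports would need to be reclassified.

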### ABG recordings

The primary outcome of this trial is the AUC of the P/F ratio. For this reason, mandatory daily ABG recordings are performed for up to 10 days after enrolment. ABGs are taken around 0600 hours and 1800 hours. The ABGs are also acquired within 60 min of any recruitment manoeuvre procedure and 30–60 min after the recruitment manoeuvre procedure. The added ABGs from RM procedures will be used in secondary analysis, but will be omitted during primary analysis to ensure the same number of data points per day for all patients.

### Duration of the intervention

Patients randomised to the model-based ventilation (MBV) cohort will remain in the protocol up to 10 days. Thereafter, they will receive the same care as participants assigned to standard practice ventilation (SPV). However, if participants have been extubated, but then require intubation and re-ventilation at any time within 10 days of enrolment, they will return to the original assigned protocol (MBV or SPV). All patients will receive standard care beyond 10 days of enrolment, and their data, including ABG recordings, will continue to be collected for up to 28 days. This intervention schedule is shown in Fig. 1.

**Fig. 1 Fig1:**
[figure not shown]
Trial assessment schedule

### General procedures

#### Procedures for the control group (SPV)

The procedures are as follows:
PEEP is selected as per standard practice.The decision to carry out a staircase recruitment manoeuvre will be based on clinical judgement. The protocol for performing the staircase recruitment manoeuvre is explained in “Recruitment manoeuvres (RM)”.ABGs will be taken twice daily.Ventilator data are collected continuously until the ventilator is disconnected.

#### Procedures for the intervention group (MBV)

The procedures are as follows:
For patients included in the MBV (intervention) group, the PEEP and MV will be guided by clinicians using bedside computers, while maintaining V_T_ and FiO_2_.Patients randomised to MBV will undergo protocolised recruitment manoeuvres (RM)
i.Before the RM, the patient should be sedated and paralysed, if required, with muscle relaxants to prevent spontaneous breathing efforts.ii.The first RM used is a maximum recruitment manoeuvre (RM_Max_). This is done at the beginning of the trial by clinicians and only repeated if clinically indicated.iii.The PEEP adjustment and monitoring procedure is referred to as a “PUMP”, whereby the PEEP is adjusted − 4 cmH_2_O to + 4 cmH_2_O of the current PEEP setting. The PUMP may be performed by ICU staff trained in this technique.The participant will no longer undergo a PUMP when:
FiO_2_ ≤ 35%,
i.And they have fully transitioned to spontaneous breathingii.And the PaO_2_ was ≥ 60 mmHg for the last 24 h, orAfter 10 days from study enrolment, orAt the discretion of the clinician, for example:
iii.When they have a new neurological condition.iv.They are awake and breathing normally without evidence of respiratory distress, and where sedation (with or without paralysis) is not considered to be in their best interests.ABGs will be recorded twice daily and before and after any recruitment procedure.Data will be collected continuously until the patient is disconnected from the ventilator.

## Recruitment manoeuvres (RM)

Patients enrolled in this study will undergo RMs. The RMs are only carried out by senior medical staff or senior trainees familiar with this technique. RM_Max_ and PUMPs are for participants randomised to the MBV protocol arm only. Patients assigned to the SPV arm may undergo a staircase RM (SRM) at the discretion of the treating clinician according to standard practice. (see “Standard practice staircase recruitment manoeuvre”).

All RMs will be performed in SIMV pressure controlled (PC) ventilation mode. The peak inspiratory pressure (Pi) is set to achieve a V_T_ of 6–8 ml/kg IBW. Preferably, V_T_ should result in DP ≤ 15 cmH_2_O above PEEP.

Before and after each RM, ABGs (pH, PaCO_2_, PaO_2_, HCO_3_), SpO_2_, end-tidal CO_2_ partial pressure (ETCO_2_), FiO_2_, PEEP, RR), and V_T_ will be recorded. In addition, during the RM_max_ (model-based ventilation arm) or (standard practice ventilation (SRM) arm, at each PEEP increment, Heart rate, rhythm, mean arterial pressure (MAP), SpO_2_, FiO_2_, V_T_, RR, ETCO_2_ and rates of use of vasoactive drugs will be recorded. This data will be valuable in assessing the safety of the RM_Max_, PUMP and SRM.

In many cases, where the lung stiffness, or respiratory elastance (E) is high, it will not be possible to deliver a V_T_ of 6 ml/kg IBW. Furthermore, during the RM, the delivered V_T_ may fall further as the elastance increases. As a result, it may be necessary to increase the respiratory rate to accommodate the reduction in minute ventilation. For example, if E is > 40 cmH_2_O/L (or compliance < 25 ml/cmH_2_O) in a patient weighing 58 kg (IBW), (normal range 15–20 cmH_2_O/L), the V_T_ will be < 6 ml/kg (< 350 ml) when the driving pressure is 15 cmH_2_O.

It is important that oxygenation targets in both arms are carefully followed to ensure a fair comparison between them. The SpO_2_ will be kept in the target range prior to any RM. This approach allows small decreases in oxygenation to be detected during the decremental PEEP phase of the recruitment manoeuvre, while also providing a sufficient buffer in the event of significant de-saturation due to ventilation perfusion (V/Q) mismatch. V/Q mismatch increases with higher airway pressures when pulmonary arterial blood is shunted away from the pulmonary capillaries by-passing aerated regions of the lung.

